# Study protocol on effectiveness of a holistic lifestyle intervention using eHealth system for older adults with metabolic syndrome and psychosomatic symptoms: a randomized controlled trial

**DOI:** 10.1186/s12877-025-06613-1

**Published:** 2025-12-29

**Keywords:** Elders, MetS, Psychosomatic symptoms, Lifestyle intervention, EHealth system, Weight loss

## Abstract

**Background:**

Metabolic syndrome (MetS) is increasingly prevalent worldwide, characterized by hormonal imbalances and psychosomatic issues that often result in chronic pain and fatigue, and are associated with a heightened risk of depression and anxiety. While previous lifestyle interventions on MetS have shown health benefits, they often lack sustainability and neglect psychosomatic aspects. This highlights the necessity for innovative treatment protocols that can address these complexities. This study aims to examine the effects of the digital Holistic Healthy Life Education (e2HLE) intervention on various outcomes among community-dwelling older adults with MetS and psychosomatic symptoms in Hong Kong.

**Methods:**

A waitlist randomized controlled trial featuring two parallel arms—an experimental group (EG) and a waitlist control group (WLCG)—will recruit 150 participants aged 60 and older with MetS and psychosomatic symptoms from five elderly centers. Participants will be randomly assigned to either the EG or WLCG. The 12-week intervention comprises weekly theme-based sessions focused on self-care, whole food plant-based diets, physical activity, self-administered acupressure, and mindfulness practices. These components are supported by an eHealth system that offers educational materials and facilitates self-monitoring of bio-signals and lifestyle changes, along with a comprehensive booklet. A two-day workshop supported by a multidisciplinary team will be conducted prior to the intervention. The intervention strategies utilize a combination of modules, incorporating in-person individual and group meetings, tele-counseling, technology-driven support groups, and buddy-assisted health coaching. A mixed-methods approach will be employed, with EG participants undergoing pretest and posttest assessments through surveys, health examinations, and blood tests, supplemented by qualitative process evaluations. WLCG participants will receive usual care for the first three months before cross over to the intervention arm. Data will be collected between baseline and the 12-week follow-up, with quantitative analysis conducted using SPSS and generalized estimating equations models.

**Discussion:**

This study is the first to investigate weight loss and alleviate cardio-metabolic risk factors and psychosomatic impacts among older adults in a Chinese context, guided by the concept of intrinsic capacity. If the intervention proves more effective than the control group, it could facilitate broader implementation in community settings and enhance theory-building and clinical practice.

**Trial registration number and date:**

ClinicalTrials.gov ID: NCT06499961. First submitted 2024-05-7.

**Supplementary Information:**

The online version contains supplementary material available at 10.1186/s12877-025-06613-1.

## Introduction

Stroke and cardiovascular disease (CVD) risk factors remain significant global health challenges [1]. Metabolic syndrome (MetS), affecting about 20.1% of the global population, is a major concern due to its strong link to CVD [2, 3]. MetS is defined as a cluster of cardio-metabolic risk factors, including diabetes, abdominal obesity, hypertension, and hyperlipidemia [4]. It reflects hormonal imbalances and psychosomatic issues [5], frequently resulting in persistent somatic symptoms such as pain and fatigue [6]. These symptoms are associated with an increased risk of depression and anxiety [7], a concern that has become particularly pronounced in the aftermath of the COVID-19 pandemic [8]. The interplay between MetS and psychosomatic symptoms presents a significant threat to health and mortality risk, deserving particular attention. Hong Kong is no exception.

Older adults in Hong Kong are living longer but with worsening health [9]. The number of individuals aged 65 and over with chronic conditions—such as hypertension, diabetes, persistent pain and depression—has nearly tripled from 340,900 in 1999 to 1.01 million in 2020/21 [10, 11]. In response, a Primary Healthcare Blueprint was created to shift from a traditional medical model to a prevention-oriented, community-based approach aimed at improving overall health [12]. This blueprint recognizes the importance of behavioral management of CVD risk factors and lifestyle modifications, aligning with the World Health Organization’s (WHO) model of healthy aging and the Integrated Care for Older People (ICOPE) framework, which focuses on enhancing Intrinsic capacity (IC) in areas like cognition, functioning, physical health, psychological well-being, nutrition and sensory capabilities [13].

## Background

Many cases of MetS stem from preventable health-related behaviors and lifestyle practices [14]. Obesity is a major component of MetS, closely linked to its other risk factors [15], making weight loss a primary treatment and prevention goal [16]. Research shows that frequent self-monitoring of food intake correlates with greater weight loss [17]. Structured behavioral interventions, involving regular support and feedback, can achieve meaningful weight loss of 5% [18], regardless of specific dietary or activity components [19]. While body weight is widely regarded as a robust indicator of MetS, other metrics like cardiopulmonary fitness and cardio-metabolic parameters should also be considered [20]. Public health concerns emphasize the need for a holistic approach addressing psychosocial and lifestyle factors in preventing and managing CVD risk [21].

Psychological distress is a significant risk factor for both MetS and CVD [22]. A meta-analysis shows that high perceived stress increases the risk of coronary heart disease (CHD) [23]. Individuals with MetS often report lower quality of life and higher depressive symptoms [24]. Increased implicit negative affect and reduced heart rate variability (HRV), which indicate heart conditions and mental health issues, are associated with a higher risk of MetS [25]. MetS also involves autonomic nervous system dysfunction, leading to insulin secretion problems and glucose intolerance, as evidenced by delayed heart rate recovery (HRR) [26]. Over half of CHD patients experience persistent somatic pain in limbs, yet treatment options are limited [27]. Given the impact of psychosocial factors and somatic symptoms on MetS and CVD, there is an urgent need for clinical trials to assess mind-body therapies [28] and to develop personalized treatment protocols for managing MetS in conjunction with psychosomatic symptoms [5].

### Whole food plant-based diets

Combining pharmacotherapy with lifestyle changes leads to greater health benefits than medical treatments alone [29]. A whole food plant-based (WFPB) diet is increasingly recognized for its role in promoting health, reducing environmental impact, and improving animal welfare [30]. Evidence links high consumption of whole plant foods to a lower risk of conditions like CVD, stroke, metabolic dysfunction, and certain cancers [31–38]. These diets also enhance emotional and physical well-being [39]. A high-quality WFPB diet is crucial for weight reduction and improving high-density lipoprotein cholesterol (HDL-C) levels [40] and may help alleviate depressive symptoms [41]. Most research treats WFPB diets as a whole, overlooking how diet quality and specific food types affect their benefits against MetS [42]. While the Mediterranean and DASH diets have been extensively studied, there is a notable paucity of randomized controlled trials evaluating the effectiveness of WFPB diets for the treatment of MetS [43].

### Physical activity

Evidence suggests that regular, moderate-intensity physical activity (PA) is strongly associated with a lower risk of MetS [44]. PA improves HDL-C and triglyceride levels [45] and is linked to better quality of life, enhanced insulin sensitivity, and improved lipid profiles. It also aids in weight loss, protects bone mass, and improves body composition [46]. Beyond physical benefits, PA enhances mental health, boosting psychological well-being and sleep quality in older adults [47]. However, a meta-review indicates that PA’s effects on other CVD risk factors are less consistent, whether used alone or with dietary apps [48].

### Self-administered acupressure

Acupressure, a non-invasive treatment from Traditional Chinese Medicine (TCM), is effective in reducing stress [49] and MetS [50], as well as significantly lowering self-rated pain and anxiety [51]. Evidence supports the effectiveness of self-acupressure for pain relief and improved sleep quality in older adults [52] and those with CHD [53]. While self-administered acupressure is gaining popularity for managing MetS and CVD risk factors, further studies are needed to confirm its effects on glycosylated hemoglobin [54].

### Mindfulness

Numerous studies show that mindfulness-based interventions effectively address psychological conditions such as anxiety, stress, chronic pain, and depression, while also enhancing overall health [55, 56]. Mindfulness has been linked to eating disorders and MetS, with higher mindfulness associated with lower obesity rates [57]. Trait mindfulness correlates with a lower prevalence of MetS in both depressive and non-depressive individuals [58]. While mind-body practices improve MetS risk factors [59], adding mindfulness to diet-exercise programs has not shown significant weight loss benefits [60]. A mindfulness app combined with a comprehensive lifestyle intervention can help control eating but has not yet significantly impacted weight loss [61].

### Lifestyle modification programs

Interventions combining PA and mindfulness have proven particularly effective in improving health outcomes and quality of life, enhancing mental health and psychological well-being more than either approach alone [62]. The ongoing U.S. multi-site enhanced life modification trial targets healthy eating, PA, and mindfulness to slow the progression of MetS. While previous lifestyle interventions for MetS have shown health benefits, these often lack sustainability, highlighting the need for innovative treatment approaches [63].

### Ehealth interventions

Structured lifestyle modification programs significantly improve health outcomes for individuals with CVD risk factors. However, simply providing information about healthy habits can sometimes lead to adverse effects, such as increased Body mass index (BMI) and blood pressure [64]. In recent years, technology-based tools for monitoring dietary and physical activity patterns have proliferated [65]. Evidence shows that eHealth interventions with app support are more effective in reducing body weight, lowering the risk of MetS progression, and promoting healthier lifestyles [66, 67]. While these interventions can reduce weight and perceived stress, their impact on diet quality and PA needs further exploration [68]. Low compliance is a common challenge in obesity management [69], and employing buddy-assisted and health coaching techniques is essential for effective multi-component interventions [70]. These findings highlight the importance of considering intervention modalities, techniques, and participant characteristics in program implementation.

In Hong Kong, community-based RCTs have demonstrated that lifestyle modification programs can lead to clinically significant weight loss of 5–10% and help prevent diabetes in overweight and obese young and middle-aged adults [71]. However, females, particularly older adults, are more prone to abdominal pain as a psychosomatic symptom [72], exacerbated by factors such as depression, anxiety, and limited vaccine doses, especially post-COVID-19 [73]. While self-administered acupressure has shown effectiveness in alleviating anxiety and pain [74], research on its physiological effects remains inconsistent [75], highlighting the need for more rigorous studies [75]. Similarly, although higher plant protein intake is linked to improved physical performance in females [76], the majority of studies have primarily concentrated on middle-aged and older adults with normal functions [77]. There is a scarcity of clinical trials in Hong Kong that evaluate WFPB diets in conjunction with IC concepts [77]. Additionally, research is limited on how MetS risk factors affect psychosomatic health and the role of interdisciplinary collaboration in multimodal lifestyle interventions aimed at reducing cardio-metabolic risks and enhancing overall well-being.

## Methods

### Study design, objective and hypotheses

This study aims to examine the effects of the e2HLE intervention, which employs a home-based self-monitoring bio-signals eHealth system (referred to as the eHealth system), on various outcomes for community-dwelling older adults with MetS and psychosomatic symptoms in Hong Kong. Figure 1 illustrates the selection of outcome measures, guided by a hypothesized pathway that integrates the multidimensional concept of IC within a multi-component evaluation framework. The protocol of the present study received approval from the university and the selected elderly centers in Hong Kong. A parallel group, 1:1 randomized controlled trial design is employed, featuring two arms: an EG and a WLCG. Given the manpower and capacity constraints at the elderly centers, this study will be implemented in a dual-stage approach, as illustrated in Fig. 2.

**Fig. 1 Fig1:**
[figure not shown]
Hypothesized pathway and outcome measures framed with the multidimensional concept of intrinsic capacity (IC) alongside a multi-component evaluation framework for the e2HLE intervention

**Fig. 2 Fig2:**
[figure not shown]
The flowchart of subject recruitment and intervention by dual

We hypothesize that EG participants will experience significant outcomes, including weight loss (primary outcome). Considering secondary outcome measures, we expect improvements in IC, focusing on the four domains, namely motor function, vitality (nutrition), psychological well-being and mental and cardiac health and enhancements in at least two cardio-metabolic risk factors, which may include waist circumference, blood pressure, BMI, visceral fat, and blood test results (such as HbA1c, LDL cholesterol levels, and homocysteine). These measures also include improvements in sleep quality and chronic pain, self-care capacity and social support, and reductions in depressive symptoms and perceived stress levels. We also conjecture that the primary effect of weight loss and secondary outcomes will be mediated by several variables, including self-efficacy, digital health literacy, mindfulness, and gerotranscendence.

### Subjects and setting

Participants will be recruited from five elderly centers using posters and briefing sessions that offer various health promotion activities for local older adults. They will learn about the e2HLE intervention aimed at reducing MetS risk factors and alleviating psychosomatic symptoms. Interested individuals will be encouraged to register, and after completing the enrolment and eligibility screening, they will receive study consent forms and an authorization letter for the use of portrait. Pre-screening and screening will determine their eligibility for participation, with criteria outlined in Appendix A. To ensure consistent implementation of this multicomponent intervention across centers, we will standardize case worker training, provide detailed manuals and guidelines, and conduct regular monitoring. The eHealth system will facilitate centralized data collection and routine audits, which will be reviewed by the project coordinator and principal investigator. Feedback mechanisms, such as debriefings and surveys, will be employed to address site-specific challenges. Collectively, these strategies are designed to minimize heterogeneity and support reliable comparisons of outcomes.

### Sample size

Based on the literature review on previous similar RCTs [63], Cohen’s d ranges from 0.2 to 0.5 for small effect and from 0.5 to 0.8 and greater than 0.8, for medium and larger effects respectively. To detect a medium effect size of 0.5, 140 participants (126/1-0.1.1.1 = 140) are required (70 participants in each arm) to achieve a statistical power of 80% at the 5% significance level (alpha = 0.05, 2 tails). Based on the attrition rate of 8% in the pilot study at 3 months that was conducted in 2021/22, it is estimated to recruit 75 participants per group (i.e. 150 in total).

### Randomization, allocation, and concealment

Eligible participants at each elderly center will be randomly assigned to either an EG or a WLCG using a computer-generated allocation sequence with a 1:1 ratio, facilitated by Research Randomizer (Research Randomizer Version 4.0; www.randomizer.org). Participants living in the same household will be randomized as a single unit to reduce the influence of their dietary habits on each other. The allocation sequence will be documented and placed in sealed envelopes, which will be opened after participants complete a baseline questionnaire. They will then be informed of their group assignment and follow-up procedures. The healthcare team and research assistants will remain blind to group allocations. All participants in the EG will receive the intervention as per the established protocol, with follow-up sessions scheduled on different dates for each group to prevent contamination and maintain blinding for assessors.

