During the process evaluation sharing sessions, EG participants will be organized into small groups of approximately 10 to 12 individuals (Table 3). Weekly individualized tele-counseling sessions by CMs, each lasting approximately 30 min, will be conducted. These sessions aim to increase motivation, review personalized care plans, and provide general support in making goal-based lifestyle changes and addressing challenges. Mutual support networking will be facilitated regularly between CMs and participants through WhatsApp or telephone communication. Each EG participant will receive a supermarket gift card valued at HKD200 (approximately USD25) as reimbursement for their time and registration fees, as well as an incentive for completing the 12-week intervention and participating in data collection.

WLCG: Participants will receive usual care from the elderly centers for the first three months. For ethical reasons, those in WLCG will crossover to the intervention arm after 12 weeks, receiving the same intervention content, dosage, and duration as the EG participants.

After completing stage one, all participants will attend a swearing-in ceremony where selected individuals will become “Smart Healthy Aging” ambassadors, coaching participants in stage two. This approach follows the Train-the-Trainer (TTT) model [80] and incorporates health coaching [69]. Key trained participants will share their insights, provide ongoing support to new participants, and facilitate the intervention process to build confidence and competence. They will receive a certificate of appreciation during the ceremony. The entire implementation process will be videotaped to create non-commercial documentary clips that aim to synthesize and disseminate evidence on the effectiveness of community-based behavior change interventions to a wider audience.

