### Planned data analysis

Data will be entered and analyzed using SPSS version 30. Demographic data will be summarized, with frequency and percentage for categorical variables, and mean and SD for continuous variables. Group difference at baseline will be compared using chi-squared tests for categorical variables and ANOVA for continuous variables. The Pearson correlation will be used to explore the relationship between weight loss and adherence scores. Changes in variables between baseline and the three-month follow-up will be compared using paired t-tests or Wilcoxon signed-rank tests as appropriate. To compare the mean changes in the continuous outcome variables including body weight, waist circumference, BMI, HRV and HRR, sleep quality, nutritional status, self-care capacity, perceived depressive symptoms and stress level, chronic pain among the two groups with the intention-to-treat principle. This approach ensures that all participants are included in the analysis as originally assigned, regardless of their level of compliance, thereby mitigating the impact of missing data. For missing values, methods like multiple imputation and sensitivity analyses will test the robustness of results. Adherence rates will also be analyzed alongside outcomes, using generalized estimating equations to account for repeated measures and reliably estimate intervention effects. Medication use for metabolic diseases and psychosomatic symptoms will be documented at baseline and follow-up, serving as a covariate in analyses to distinguish intervention effects. Subgroup analyses may compare outcomes between medicated and non-medicated participants. As age may significantly influence participants’ responsiveness to the intervention, conducting subgroup analyses by age cohort offers more specific insights into how the intervention may benefit older adults at different stages of aging. Post hoc pairwise comparisons of the changes in the outcome variables across the two study groups will be performed to compare the effectiveness of the EG and the WLCG. All the tests are two-sided and a *p* < 0.05 will be considered statistically significant.

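### Co-habiting participants are randomised as one unit within centres, but the stated analysis names neither household nor centre, so its standard error does not match the randomisation

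*Protocol article*

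**What the plan says.** Under Randomization, allocation, and concealment, the article says: "Eligible participants at each elderly center will be randomly assigned to either an EG or a WLCG using a computer-generated allocation sequence". The ratio is 1:1, and Subjects and setting gives five centres. The same section adds: "Participants living in the same household will be randomized as a single unit to reduce the influence of their dietary habits on each other".

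Planned data analysis is the place where the model is described. GEE appears there with one stated purpose: "using generalized estimating equations to account for repeated measures and reliably estimate intervention effects". Medication use is the covariate named in that section. Validity and reliability adds a general promise to account for baseline differences between groups. Household and centre are not named in either place.

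Sample size gives "140 participants (126/1-0.1.1.1 = 140) are required (70 participants in each arm") for a standardised effect of 0.5, 80% power and a two-sided 5% test, and then a recruitment target of 150 with 8% attrition cited from the pilot. It mentions no intraclass correlation and no design effect.

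Under Intervention protocol, the experimental group (EG) attends nine theme-based sessions and three sharing sessions. For the sharing sessions, "EG participants will be organized into small groups of approximately 10 to 12 individuals". The waitlist group receives usual care over the same 12 weeks.

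**The concern.** The reason given for keeping household members together is that they influence each other's diet. In a dietary trial with body weight as primary outcome, that is also a reason to expect their outcomes to be correlated. Members of one household always land in the same arm, so positive correlation between them adds variance to the treatment contrast. GEE clustered on the participant handles the baseline and follow-up values of one person but treats two spouses as independent. Its standard error is then too small and the test slightly liberal.

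Centre raises the same mismatch in the opposite direction. If allocation is balanced within centre and centre affects the outcome, leaving centre out keeps between-centre variation in the residual and makes the standard error too large.

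At stake is whether the confidence interval and p-value for the primary comparison reflect the way participants were actually allocated.

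**Working it through.** **1. The plan's own figure.** Inputs from Sample size: d = 0.5 (SD = 1), two-sided alpha 0.05, power 80%.

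- n per arm = 2(1.960 + 0.842)²/0.5² = 62.8, rounded up to 63, so 126 in total.
- 126/(1 − 0.10) = 140. The printed expression is garbled, but 140 reproduces exactly in this way.
- Both numbers are those for independent individuals. No clustering allowance is built in.

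**2. Power at the recruitment target, under independence.** 150 × 0.92 = 138 evaluable, or 69 per arm. Power = Φ(0.5/√(2/69) − 1.96) = 83.6%.

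**3. Household clustering.** The article gives neither the share f of participants enrolled as household pairs nor the within-pair correlation ρ, so both are assumed. A pair contributes 2(1 + ρ) to the variance of a sum where two independent people contribute 2. The design effect is therefore DE = 1 + fρ. The true type I error of a nominal 5% test that ignores it is 2[1 − Φ(1.96/√DE)]. Power at 69 per arm is Φ(0.5/√(2·DE/69) − 1.96).

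| f | ρ | DE | SE understated by, 1 − 1/√DE | Type I error | Power, 69 per arm |
|---|---|---|---|---|---|
| 0.10 | 0.3 | 1.03 | 1.5% | 5.3% | 82.5% |
| 0.20 | 0.5 | 1.10 | 4.7% | 6.2% | 80.0% |
| 0.30 | 0.5 | 1.15 | 6.7% | 6.8% | 78.2% |

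**4. Centre.** Assume that allocation is stratified by centre and that centre explains 5–10% of outcome variance (again not in the article). Omitting it makes the standard error too large by 1/√(1 − 0.05) = 1.03 to 1/√(1 − 0.10) = 1.05, that is by about 3–5%.

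**5. The two together.** Multiplying the factors as an approximation, the ratio of true to reported variance runs from 1.03 × 0.90 = 0.93 to 1.15 × 0.95 = 1.09. The range includes 1, so the sign of the net error cannot be settled from the article.

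**6. How much inflation the sample size absorbs.** Power is 80% when 69/DE = 62.8, so DE = 69/62.8 = 1.10.

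**7. Group delivery in EG.** For groups of size m in one arm only, the average inflation is {[1 + (m − 1)·ICC] + 1}/2. With m = 11 and an assumed ICC of 0.01–0.05, this is 1.05–1.25, with type I error 5.6–8.0% and power at 69 per arm from 81.8% down to 74.8%. These values are illustrative only. The article gives no ICC, and the size of 10 to 12 belongs to the three sharing sessions. The group size for the nine theme sessions is not stated, nor is the number of participants per case manager.

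**The case against.** **The article is condensed.** The GEE cluster level and the full covariate list are often left to an analysis plan, and none is shown. Planned data analysis does not say that the participant is the only cluster or that medication is the only covariate. That stands as a caution: a fuller plan may already deal with the point. It does not remove the point, because the article does state the randomisation unit, the purpose of the GEE and a sample size based on independence, and the last two do not reflect the first.

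**Few participants may be affected.** The household rule applies only to people who live with another enrolled participant. Everyone else is randomised individually, and the number of pairs is unknown. This stands, and it is why the household effect is modest even under the assumed ranges.

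**Stratification by centre is a reading.** The text speaks of assignment at each centre but of one allocation sequence. If centre is not a stratum, leaving it out does not make the standard error too large. This stands, and the centre statement is conditional for that reason.

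**Stronger readings that the article does not support.** A reader might infer that the stated power is overstated. Under independence, 138 evaluable participants give 83.6% against the 80% claimed, and nothing in the article shows total inflation above 1.10. A reader might also take the 8.0% type I error and 75% power from step 7 as the expected size of the problem. They apply the sharing-session group size to an intervention that also includes individual tele-counselling, home self-monitoring and individual blood-report sessions. They also concern groups used to deliver treatment, which is separate from the unit of randomisation.

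**Conclusion.** The mismatch is real and modest. Taken as written, the analysis does not reflect the units, and probably the strata, used in randomisation. Household correlation alone would take a nominal 5% test to about 5.3–6.8%, on the assumption of 10–30% of participants in pairs and a correlation of 0.3–0.5. Omitting centre, if it is a stratum, pushes the other way by about 3–5% of the standard error, so the net direction is unknown. It would go too far to call the primary p-value invalid or to say that the trial misses its 80% power. What can be said on power is that the stated 80% assumes independent participants and, with about 138 evaluable, survives a total design effect of up to about 1.10. Any effect of group delivery in EG cannot be sized from the article.

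**What to change.** - **Planned data analysis:** define the GEE cluster as the household, with robust standard errors. A participant living alone, or with no co-enrolled household member, forms a cluster of one. Include centre as a fixed factor; five centres are too few to serve as GEE clusters.
- **Optional sensitivity analysis:** a mixed model with a random group or case-manager effect in EG only.
- **Sample size:** say that the 80% power assumes independent participants, and that with about 138 evaluable it holds up to a total design effect of about 1.10.
- **Data collection:** record household, group and case-manager IDs at enrolment and group formation, since they may be hard to recover later.

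The cost is a few degrees of freedom for centre, the extra ID fields, and a slightly more guarded power statement.
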